### Procedure for unblinding if needed {17b}

The design is open label, and only the statisticians will be blinded until the end of the analysis; thus, unblinding will not occur.

### Study intervention {11a}

Two neurologists and six examined acupuncturists (four licensed physicians with experience in TCM- research and two doctoral students with diplomas for acupuncture and 140 h of acupuncture training) are presently recruiting and treating patients. The choice of acupuncture points was made via discussion with six acupuncture experts from the following two major German societies for medical acupuncture: the German Medical Acupuncture Association (*Deutsche Ärztegesellschaft für Akupunktur*; DÄGfA), Munich, and the International Society for Chinese Medicine (*Societas Medicinae Sinensis,* SMS), Munich. The ultimate strategies were generally considered a pragmatic compromise between the need for standardization in science and the need for individualization in Chinese medicine. Furthermore, the rationale of the acupuncture- point selection was furthermore supported by the treatment strategy provided in a pilot study from Meyer-Hamme et al. [16]. The acupuncture treatment consists of 12 sessions administered over a period of 8 weeks (preferably 2 sessions in each of the first 4 weeks, followed by 1 session per week in the remaining 4 weeks). The acupuncture treatment in the ACUDPN study is semi-standardized (Table 2) as follows: all patients must be treated at the basic obligatory acupuncture points, i.e., bilaterally ST34, ST40, SP6, Ki 3, and LV3, and bilaterally at the EX-LE-10 Bafeng points, which sum up to 18 needles per session (see Fig. 2).

**Fig. 2 Fig2:**
[figure not shown]
Obligatory acupuncture points used in the ACUDPN study (modified from Stux, G. Akupunktur Lehrbuch und Atlas, Springer Verlag Berlin Heidelberg, 2008 with permission)

**Table 2 Tab2:** Acupuncture points used in the ACUDPN study

**Obligatory points**	ST 34, ST 40, SP 6, KI 3, LV 3, EX-LE-10 Bafeng
**Optional points depending on the following Chinese medicine diagnoses**	
Cold invasion into meridians	Moxa on EX-LE-10 Bafeng, KI 3
Deficiency of qi and xue	ST 36, GB 39, ST 41 (in pronounced sensory ataxia)
Qi-stagnation and blood stasis	GB 34, GB 40, SP 4
Wind and phlegm block channels	ST 36, SP 9, SP 4
Phlegm and heat block channels	SP 9, SP 10, GB 40, KI 7

Furthermore, at least 2 of 10 facultative acupuncture points will be selected according to the patient’s individual constitution and disease pattern following the diagnostic principles of Chinese medicine {11b}. The acupuncture points used in a session will be documented each time. A diagnosis of traditional Chinese syndrome at baseline is mandatory, and the diagnosis will be documented. Patients will lie down in supine position. Needles will be inserted perpendicularly and stimulated only in the beginning to achieve a DeQi sensation and then will be left in place without further stimulation for 20–25 min.

The duration of 12 acupuncture sessions within one treatment cycle with 1–2 sessions per week and between 20 and 30 min per session is supported by common textbooks for acupuncture and taught in acupuncture schools internationally. The needle length and diameter will be chosen according to the anatomical location and constitutional picture. If numbness is present, superficial puncture with a sharp needle will be carried out at the Bafeng points, and tiny amounts of blood will be released twice during the treatment period. In both groups, moxibustion is allowed and will be applied by using a common moxibustion TDP- lamp (Phoenix Bio TDP CE005) exclusively at the feet over 15 min at 20 cm distance to the toes, in case of cold and numb feet. Since the focus is on body acupuncture, we excluded auricular acupuncture strategies.

The patients in the control group will not receive acupuncture treatment for a period of 16 weeks after randomization. During this period, the patients in the control group will participate in follow-ups only with the use of diaries and questionnaires. After 16 weeks, the patients in this group will receive the same acupuncture treatment according to the principles described above.

The patients in both groups will be allowed to continue routine care medication (if applicable), which will be adapted as needed during the study.

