**Methods:**

This study is a two-armed, randomized, controlled, parallel group, open-label, confirmatory, multicenter trial (8-week intervention period plus 16 weeks of follow-up). Physicians in outpatient units in Germany who specialize in acupuncture treatment will treat 110 diabetes type II patients with clinical symptoms of peripheral neuropathy in the feet and legs with signs of neuropathy according to nerve conduction testing. The patients will be randomized in a 1:1 ratio to one of the following two groups: (a) semi-standardized acupuncture plus routine care or (b) routine care alone. Acupuncture will consist of 12 treatments per patient over 8 weeks. The primary outcome will be the overall DPN-related complaints in the extremities after 8 weeks as measured by the Visual Analog Scale (VAS). Further outcome measures will include DPN-related pain, the Neuropathic Pain Symptom Inventory (NPSI), Diabetic Peripheral Neuropathic Pain Impact (DPNPI) scores, and nerve conduction parameters of the sural nerve at weeks 8, 16, and 24.

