## Methods: participants, interventions, and outcomes

### Study setting {9}

This study is being conducted in Germany. The main recruiting center is located in Berlin at the Charité University Hospital, and another recruiting center is located in Hamburg in a research and treatment center for traditional Chinese medicine. The overall study duration per patient is 24 weeks. After randomization at baseline, the patients in the acupuncture group will undergo 12 treatment sessions in addition to routine care during the first 8 weeks of the study, followed by 16 weeks of follow-up. In the control group, all patients will continue to receive routine care and undergo several study follow-up examinations during the first 16 weeks. In this control group, patients are on a waiting list for the acupuncture treatment, which will be started at week 16 and continued until the final follow-up at week 24 using the same acupuncture treatment protocol being performed in the other study arm (see Fig. 1 and Table 1).

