### Outcomes {12}

The primary outcome parameter in the ACUDPN study is the overall DPN-related complaints at week 8 measured on a 0–100 mm VAS (0 = no complaints, 100 = worst imaginable complaints).

The VAS is a well-established and validated assessment tool that has been used in several clinical studies in conventional medicine and complementary medicine, e.g., acupuncture [11, 17], as a primary or secondary outcome measure.

Responders to the study intervention will be defined as patients with an overall change in DPN-related complaints of 15 mm or more between the VAS at baseline and the VAS in week 8.

The secondary outcome measures include the overall number of DPN-related complaints at week 16 and week 24 (VAS); the pain intensity at weeks 8, 16, and 24 (VAS); and the Neuropathic Pain Symptom Inventory (NPSI) score at weeks 8, 16, and 24. The NPSI scores subdimensions of neuropathic pain, such as spontaneous ongoing or paroxysmal pain, evoked pain (i.e., mechanical and thermal allodynia/hyperalgesia), and dysesthesia/paresthesia, using an 11-point scale [18].

Since numbness is not assessed in the NPSI, we added the 11-point NRS scale for numbness (0 = no numbness at all to 10 = no sensation on the soles of the feet).

The Diabetic Peripheral Neuropathic Pain Impact (DPNPI) measure is a validated tool used to assess the disease-specific impact on the quality of life [19] and will be applied at the abovementioned time points in addition to a general health-related quality of life assessment using the SF-12 [20].

The German questionnaire on emotional pain perception *Schmerz Empfindungs Skala* (SES) will be used to monitor the effect of acupuncture on the affective components of pain [21] following a timely schedule as described above, i.e., at baseline and weeks 8, 16, and 24.

The Patient Global Impression of Change (PGIC) scale consists of a patient assessment from 0 = much worse to 7 = much better [22] and will be measured only at weeks 8, 16, and 24.

Further secondary outcome parameters are the general clinical and neurological presentation registered with the Neuropathy Deficit Score (NDS) [23] and the clinical Total Neuropathy Score (cTNS) [24]; these assessments will be noted as described above at baseline and weeks 8, 16, and 24. Adverse events, dropouts, withdrawals, and the respective reasons will be documented.

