#### Plans to promote participant retention and complete follow-up {18b}

Protocol deviations are documented on a separate list. The patients have been informed of the value of completing the study course. The patients receive reminding phone calls if they miss an acupuncture treatment or a questionnaire has not been returned in time. If a patient drops out of treatment, it will be documented on a special study discontinuation form, and the patient will be motivated to continue to complete the questionnaires. After receipt of the final questionnaire, the patients will be reimbursed for transportation fees to the study site for the 12 acupuncture sessions and 2 follow-up examinations with the lump sum of 60€.

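### The intervention section limits control follow-up to diaries and questionnaires for 16 weeks, contradicting the examinations that other sections schedule in that period

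*Protocol article*

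**What the plan says.** The control arm's follow-up before its own acupuncture is described twice.

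- Study intervention {11a}, in the text after Table 2, first sets the period: "The patients in the control group will not receive acupuncture treatment for a period of 16 weeks after randomization". It then says how controls are followed in that time: "the patients in the control group will participate in follow-ups only with the use of diaries and questionnaires".
- Study setting {9} says of the control group that "all patients will continue to receive routine care and undergo several study follow-up examinations during the first 16 weeks". Control acupuncture starts at week 16 and runs to the final follow-up at week 24.

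The examiner-based outcomes are scheduled elsewhere, with no restriction by arm.

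- The Abstract (Methods) lists "nerve conduction parameters of the sural nerve at weeks 8, 16, and 24".
- Outcomes {12} says of the NDS and the cTNS that "these assessments will be noted as described above at baseline and weeks 8, 16, and 24".
- Plans for the assessment and collection of outcomes {18a} assigns the neurological examinations and the electrophysiology to two neurologists, while questionnaires and diaries travel by mail.
- Statistical methods {20a} analyzes secondary outcomes with between-group models (ANCOVA or logistic regression) that include treatment group, center and, where applicable, the baseline value.

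The retention section {18b} also mentions a travel lump sum covering "12 acupuncture sessions and 2 follow-up examinations".

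**The concern.** The word *only* in the intervention section excludes examinations for the same arm and period in which the setting section provides them. This is not a detail that an article leaves to the full protocol: the article states the rule twice, in incompatible ways.

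The weeks before control acupuncture are the only ones in which a randomized comparison of acupuncture plus routine care against routine care alone exists. Sural velocity and amplitude, the NDS and the cTNS depend on both arms being examined in that window. Neurophysiological outcomes are named in Objectives {7}, and the Discussion expects the trial to bear on whether acupuncture has neuroregenerating effects. The trial is open-label and its primary outcome is self-reported, so the device-based nerve measurement is among its least subjective evidence.

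The practical risk is uneven. Acupuncture patients are on site for treatment until about week 8. Waiting controls have no treatment visits, so a center that relies on the intervention section has no other occasion to examine them.

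**Working it through.** **Number of controls concerned.** Sample size {14} gives a difference of 15 mm, SD 25 mm, two-sided alpha 0.05 and 80% power.

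- Standardized difference: 15/25 = 0.6. The two-sided t test needs 44.6, that is 45 per group, with power 80.4% at 45. The stated 90 reproduces.
- Dropout: 90/(1 − 0.15) = 105.9, so 106. The stated 110 allows for 1 − 90/110 = 18.2% and is on the safe side.
- Controls: 110/2 = 55 randomized and 45 expected evaluable.

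These figures are context only. The point rests on setting the sections side by side.

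| Time point | Examiner-based outcomes scheduled | Study setting {9}, controls | Study intervention {11a}, controls | Control status |
|---|---|---|---|---|
| Baseline | Yes | Before the period | Not restricted | Untreated |
| Week 8 | Yes | Within the period with examinations | Diaries and questionnaires only | Untreated |
| Week 16 | Yes | End of the period with examinations | Restricted if the visit counts as inside the 16 weeks | Untreated only if examined before the first session |
| Week 24 | Yes | After the period | Not restricted | Acupuncture since week 16 |

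**Consequence if the intervention section is followed.**

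1. At week 8, 0 of 45 evaluable controls (0 of 55 randomized) have sural velocity, sural amplitude, NDS or cTNS.
2. At week 16 the count is also 0 if that visit falls inside the period. The text does not settle this.
3. A between-group ANCOVA needs post-baseline values in both arms. With none in one arm, the treatment effect cannot be estimated at that time point, whatever was measured at baseline.
4. Week 24 has data in both arms, but it compares patients 16 weeks after their acupuncture period (24 − 8) with patients at the end of theirs. That contrasts early with delayed acupuncture, not acupuncture with routine care.

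**Consequence if the setting section is followed.** Controls are examined, and the comparison can be made at week 8 and, with the right ordering of visits, at week 16.

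**Room to correct.** Trial status reports 62 patients included on Jan 5, 2021. That leaves 110 − 62 = 48 still to be enrolled, in addition to any enrolled patients whose examinations are still ahead.

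**The case against.** The strongest reply is that this is a drafting slip. The sentence stands in the intervention section, where its purpose is to say that waiting controls get no acupuncture. Study setting {9}, the Abstract, Outcomes {12} and the data-collection section all point to examinations in both arms. Fig. 1 and Table 1 hold the participant timeline, and their captions list a neurological examination with the cTNS. Both are missing from the text available here and may settle the schedule by arm. This argument stands as far as intent goes: examinations of controls are probably intended. It does not remove the contradiction, because a center can still act on the sentence as written.

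It is also fair to say that the stakes are limited. The primary outcome is the week 8 VAS, which patients report themselves, and all other analyses are declared exploratory.

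Three stronger readings are tempting, and the document does not support them.

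- A reader might infer that controls would have no examination data at all. The restriction covers only the 16 weeks after randomization, so baseline and week 24 remain open.
- A reader might infer from the two reimbursed examinations, against three scheduled follow-up time points, that one third of the examinations are not provided for. The lump sum is not a visit schedule. An examination on the day of an acupuncture session would need no separate journey, and the text does not say whether such visits coincide. It does not suggest either that the two examinations fall in different weeks in the two arms.
- A reader might conclude that week 24 should be dropped for these outcomes. That would remove the acupuncture arm's longer-term neurophysiological follow-up, and the longer follow-up is a stated feature of the trial.

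**Conclusion.** The contradiction is real and should be corrected. Study intervention {11a} excludes what Study setting {9} provides and what the Abstract, Outcomes {12} and the data-collection section require. If the intervention section is followed, there are no examiner-based data from untreated controls at week 8 (0 of 45 evaluable) and arguably none at week 16. The acupuncture against routine care comparison is then lost for sural velocity and amplitude, the NDS and the cTNS.

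The size of the loss is conditional. It assumes that a center applies the sentence literally, and for week 16 that the visit counts as inside the 16 weeks. If the setting section governs practice, nothing is lost and the fault is one of wording. The document does not show which has happened. Confidence is therefore high in the contradiction and lower in the consequence. Control data at baseline and week 24, the primary analysis and the sample size are not affected.

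**What to change.** - Correct the sentence in Study intervention {11a} so that both arms have the neurological examination and the sural nerve measurement at weeks 8 and 16, as already scheduled.
- State that the control examination at week 16 takes place before the first control acupuncture session, so that it still reflects routine care alone.
- Keep week 24 for these outcomes, and describe it as a time point at which both arms have had acupuncture.
- Align Study setting {9} by naming the examination weeks for each arm, and check that Fig. 1 and Table 1 agree.
- Say in {18b} which two examinations the travel reimbursement refers to.
- Ask both centers which control examinations have been done so far. If week 8 or week 16 measurements were not taken, report how many are missing by arm and center.

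The cost is a wording change and one query to each center. It adds no visits beyond those already scheduled. Missed control examinations cannot be recovered, but the correction would still protect the 48 patients not yet enrolled at the reported status date.

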#### Explanation of the choice of comparators {6b}

To determine whether acupuncture has overall effects on DPN, we compare acupuncture plus routine care versus routine care in this confirmatory trial. If we yield positive results, acupuncture should be compared in another clinical trial with sham acupuncture to study the specific effect of acupuncture.

#### Criteria for discontinuing or modifying the allocated interventions {11b}

If a patient wishes to drop out, serious side effects occur, or any circumstances place the patients’ health at hazard, the physician will discontinue the treatment. The allocated interventions will not be modified.

#### Strategies to improve adherence to interventions {11c}

Adherence to treatment requires the physical presence of the patient. The phone numbers of the patients have been registered. If a patient does not show for an appointment or does not return the questionnaires or the questionnaires are incomplete, the study nurse will contact the participant. If necessary, a treating physician will speak with the participant.

#### Relevant concomitant care permitted or prohibited during the trial {11d}

Permitted concomitant care comprises all drug prescriptions for DPN pain, except for drugs belonging to complementary medicine (i.e., traditional Chinese herbs). The prohibited care includes the uptake of new physiotherapeutic or psychotherapeutic measures aiming to ease DPN-related discomfort.

#### Provisions for post-trial care {30}

Both trial centers’ insurance will compensate for those who suffer harm from trial participation.

### Outcomes {12}

The primary outcome parameter in the ACUDPN study is the overall DPN-related complaints at week 8 measured on a 0–100 mm VAS (0 = no complaints, 100 = worst imaginable complaints).

The VAS is a well-established and validated assessment tool that has been used in several clinical studies in conventional medicine and complementary medicine, e.g., acupuncture [11, 17], as a primary or secondary outcome measure.

Responders to the study intervention will be defined as patients with an overall change in DPN-related complaints of 15 mm or more between the VAS at baseline and the VAS in week 8.

The secondary outcome measures include the overall number of DPN-related complaints at week 16 and week 24 (VAS); the pain intensity at weeks 8, 16, and 24 (VAS); and the Neuropathic Pain Symptom Inventory (NPSI) score at weeks 8, 16, and 24. The NPSI scores subdimensions of neuropathic pain, such as spontaneous ongoing or paroxysmal pain, evoked pain (i.e., mechanical and thermal allodynia/hyperalgesia), and dysesthesia/paresthesia, using an 11-point scale [18].

Since numbness is not assessed in the NPSI, we added the 11-point NRS scale for numbness (0 = no numbness at all to 10 = no sensation on the soles of the feet).

The Diabetic Peripheral Neuropathic Pain Impact (DPNPI) measure is a validated tool used to assess the disease-specific impact on the quality of life [19] and will be applied at the abovementioned time points in addition to a general health-related quality of life assessment using the SF-12 [20].

The German questionnaire on emotional pain perception *Schmerz Empfindungs Skala* (SES) will be used to monitor the effect of acupuncture on the affective components of pain [21] following a timely schedule as described above, i.e., at baseline and weeks 8, 16, and 24.

The Patient Global Impression of Change (PGIC) scale consists of a patient assessment from 0 = much worse to 7 = much better [22] and will be measured only at weeks 8, 16, and 24.

Further secondary outcome parameters are the general clinical and neurological presentation registered with the Neuropathy Deficit Score (NDS) [23] and the clinical Total Neuropathy Score (cTNS) [24]; these assessments will be noted as described above at baseline and weeks 8, 16, and 24. Adverse events, dropouts, withdrawals, and the respective reasons will be documented.

In addition, the patients will be requested to complete patient diaries following a daily schedule, which will include recording on-demand medication use, a weekly assessment of the average VAS score of pain, and the overall number of DPN-related complaints during the first 8 weeks and at weeks 15 to 16 and 23 to 24.

The neurophysiological parameters will include measurements of the sural nerve. This nerve is pathognomonically affected in diabetic neuropathy and is used to monitor peripheral neuropathy. The nerve conduction velocity and amplitude of sensible action potentials will be measured with a novel point-of-care nerve conduction device (POCD) produced by NeuroMetrix™, Texas. This device is used in the DPNCheck®, which provides accurate, cost-effective, and quick screening data for the diagnosis and monitoring of diabetic peripheral neuropathy (DPN). With a 10-s period of measurement, this device can provide the numeric values of velocity (m/s) and amplitude (μV). This device has been validated in several studies as an accurate screening and monitoring instrument for DPN and the evaluation of the risk of diabetic foot [25–27].

TCM-related indexes as outcomes are not used in this trial.

### Data collection and management

#### Plans for the assessment and collection of outcomes {18a}

The baseline and follow-up neurological examinations, including the electrophysiological data collection, will be performed by two neurologists. These neurologists do not perform any acupuncture treatments. Each acupuncture treatment is documented by trained acupuncturists; the needles at mandatory and facultative points and their mode of application (i.e., stimulating or sedating technique) are noted and counted.

Medication will be listed on a medication log; any changes in pain-modifying drugs will be noted on a weekly basis in the diaries. At the baseline visit, the patients are given diaries that they take home for the first 8 weeks, and weekly outcomes are to be noted in these diaries. Every 8 weeks, via mail, the patients receive another set of questionnaires to assess the abovementioned outcomes. The diaries and questionnaires must be returned in the envelopes provided by the study center.

To prevent loss by mail, data sheets of the baseline examination are provided in duplicates; one copy remains at the study site. Upon receipt of the baseline and follow-up case report forms and the patients’ diaries and questionnaires at the main study center at the Charité University Hospital, the monitoring study staff checks for the completeness of the data. The responsible physician will be notified of any missing data from the physical or neurological evaluation within the next working day. All questionnaires and dairies are transmitted via mail; the delayed return of the questionnaires will be followed by a reminder phone call to the patient. Missing outcomes in the questionnaires will be completed by contacting the patients and sending the patients a copy of the incomplete questionnaire or isolated questions via mail.

